#### Concealment mechanism {16b}

The randomized results will be securely sealed in opaque envelopes and stored separately until the end of the study. To maintain unbiased assignment and minimize potential confounding factors, the investigators responsible for generating the random sequences will not be involved in recruitment, anesthesia administration, and outcome evaluation. Preoperative interview researchers, unaware of the random allocation number, will screen and recruit participants and completed the QOR-40 scale 1 day before surgery [13].

#### Implementation {16c}

As soon as the patients enters the operation room, the attending anesthesiologist will open the corresponding numbered envelope, verify the patient’s allocation, and proceed to implement the corresponding anesthesia plan accordingly.

### Assignment of interventions: blinding

#### Who will be blinded {17a}

Due to the nature of the study, blinding of the attending anesthesiologist is not feasible. However, patients, outcome assessors, surgeons, and nursing staff will remain blinded until the completion of the study analysis.

#### Procedure for unblinding if needed {17b}

While we do not anticipate the need for unblinding, if necessary, such as the occurrence of a research-related serious adverse event, the principal investigator or data manager will have access to the group assignment and will report any unblinding promptly.

### Data collection and management

#### Plans for assessment and collection of outcomes {18a}

Research data for this study will be collected from electronic medical records systems or case report forms (CRFs). Preoperative data, including demographics, medical history, medication history, supplementary examinations, and preoperative assessment, will be completed by preoperative visitors. The anesthesiologist will record intraoperative data. The QOR-40 scale 1 day before surgery and postoperative outcomes assessment will be collected by a dedicated assessor. To ensure scientific rigor of our study, all researchers will be trained on how to collect, record, and store data before the trial starts. All information will be strictly confidential and used solely for research purpose. After data collection, it will be double-entered into Microsoft Excel system and check by two researchers. The principal investigator will conduct a thorough check for any defects in the raw data again. Participants’ personal information will be kept confidential.

#### Plans to promote participant retention and complete follow-up {18b}

During the preoperative visit, researchers will provide detailed explanation of the intraoperative management and postoperative follow-up process.

#### Data management {19}

All data will be anonymized, with CRFs abbreviated as initials, and electronic data is coded. Electronic data will be stored on a dedicated computer with double password protection, while paper CRFs will be securely stored in our research center with password-locks. All original documents will be retained for 5 years after the study is completed.

#### Confidentiality {27}

Patients will continue to be enrolled until the required number is reached. All data will be anonymized, with CRFs abbreviated as initials, and electronic data is coded. All original documents will only be accessible to researchers with the original ID and password.

#### Plans for collection, laboratory evaluation, and storage of biological specimens for genetic or molecular analysis in this trial/future use {33}

Not applicable. No samples will be collected for this study.

### Statistical methods

#### Statistical methods for primary and secondary outcomes {20a}

All normally distributed continuous variables will be expressed as mean ± standard deviation and analyzed with Student’s *t*-test. For non-normal distributed data, the Mann–Whitney *U* test will be used, and results will be presented as median and interquartile interval. Categorical variables will be described with frequencies (%) and compared using the chi-square test or Fisher’s exact test. A 95% confidence interval (CI) for differences in means (for continuous outcomes) or relative risks (for categorical outcomes) will be calculated. A *P* value < 0.05 will be considered statistically significant. Statistical analyses will be performed using SPSS software version 26 (IBM, New York, USA).

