Furthermore, the integration of multimodal analgesia with regional block technique can improve analgesic efficacy while mitigating the adverse effects associated with opioid analgesics. However, achieving meaningful clinical outcomes require optimal postoperative recovery. Anesthesia and postoperative recovery constitute a multidimensional and intricate process. The QOR-40 scale is widely utilized in clinical settings to evaluate early postoperative recovery quality following anesthesia and surgery. Recognized for its suitability, feasibility, effectiveness, reliability, and precision, the QOR-40 scale is considered an optimal standard for assessing postoperative recovery [11]. Additionally, researchers have identified that preoperative low QoR-40 scores can predict poor postoperative recovery, and early effective interventions can enhance postoperative recovery quality, thus improving patient quality of life [12]. Therefore, establishing a direct correlation between ultrasound-guided SAPB and post-transapical TAVI surgery recovery quality necessitates further prospective data.

Our study seeks to examine the impact of ultrasound-guided SAPB on early postoperative recovery quality and analgesic efficacy in patients undergoing transapical TAVI procedures. By refining further multi-mode analgesia and ERAS protocols of this surgery, we aim to improve the postoperative rehabilitation quality and optimize the utilization of medical resources.

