### Sample size {14}

The sample size calculation is based on the primary outcome. According to a prior publication, where mean of group 1 was 167 and the mean of group 2 was 184, with known group standard deviations of 23 [13], a sample size of 33 for each group (66 in total) will be required to achieve a power of 80% to detect the difference at a two-side *α* level of 0.05, taking into account a dropout rate of 10%. Ultimately, we plan to include 35 participants in each group.

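### The stated QoR-40 analysis leaves out a baseline score that is collected in every patient and called predictive, and its normality-dependent rule leaves the primary test open and can pair a rank-test P value with a confidence interval for means

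*Protocol article*

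**What the plan says.** The Outcomes section {12} makes QoR-40 at 24 h and 48 h the primary outcome. Table 1 schedules the same scale at −1 day. Section {16b} confirms this: the preoperative researchers "will screen and recruit participants and completed the QOR-40 scale 1 day before surgery". The background {6a} gives a reason to value that measurement: "preoperative low QoR-40 scores can predict poor postoperative recovery".

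Section {20a} covers primary and secondary outcomes together and gives one rule for all continuous variables: "All normally distributed continuous variables will be expressed as mean ± standard deviation and analyzed with" Student's t-test. Data judged non-normal go to Mann–Whitney U and are summarised by median and interquartile interval. The section then promises, for continuous outcomes without distinction, "A 95% confidence interval (CI) for differences in means (for continuous outcomes" and so on. Baseline QoR-40 appears in neither branch. Sections {20b}, {20c} and {21b} add no adjusted analysis.

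Section {14} sizes the trial on a difference in means: "mean of group 1 was 167 and the mean of group 2 was 184", "with known group standard deviations of 23", two-sided 5% level, 80% power, 10% dropout. It states 33 per group and plans 35.

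**The concern.** Two separate matters arise from the same paragraph.

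**Baseline not used.** A preoperative score on the outcome scale is usually the most natural covariate, and this protocol itself describes it as predictive. If it is left out, the variance it explains stays in the error term, and a chance baseline difference between two arms of 35 is carried into the estimate in proportion to the correlation. What is at stake is the width of the confidence interval and the power margin.

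**Test chosen by the observed distribution.** The primary test is not known until the outcome data have been examined. If the rank branch is taken, the P value concerns a comparison of ranks while the promised interval concerns a difference in means. The two can then point different ways for the primary outcome, and the rank branch departs from the quantity on which the trial was sized.

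**Working it through.** **Inputs from section {14}.** Difference 184 − 167 = 17; SD 23; two-sided α 0.05; power 80%; dropout 10%; 35 per arm planned. The correlation r between baseline and postoperative QoR-40 is not in the protocol, so a range is assumed.

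**Step 1: the plan's own figure.** By the normal approximation, n = 2 × [23 × (1.960 + 0.842)/17]² = 28.7, so 29 per arm. 29/0.9 = 32.2, so 33 per arm, as stated. The exact t-test needs 29.7, so 30 per arm, and 30/0.9 = 33.3 gives 34. Both lie within the 35 planned. The sample size reproduces and corresponds to an unadjusted comparison of means.

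**Step 2: unadjusted power.** Evaluable per arm: 35 × 0.9 = 31.5. Standard error = 23 × √(2/31.5) = 5.80. Noncentrality = 17/5.80 = 2.93 on 61 degrees of freedom. Power is 82.3%.

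**Step 3: power with baseline adjustment.** Residual SD = 23 × √(1 − r²). The equivalent sample-size factor is 1/(1 − r²). The 95% half-width is about 2.00 × residual SD × √(2/31.5).

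| r (assumed) | Residual SD | Power, 31.5 per arm | Power, 35 per arm | Half-width, 31.5 per arm | Size factor |
|---|---|---|---|---|---|
| 0 (unadjusted) | 23.0 | 82.3% | 86.2% | 11.6 | 1.00 |
| 0.2 | 22.5 | 83.8% | 87.5% | 11.4 | 1.04 |
| 0.3 | 21.9 | 85.7% | 89.2% | 11.1 | 1.10 |
| 0.5 | 19.9 | 91.5% | 94.1% | 10.0 | 1.33 |
| 0.6 | 18.4 | 95.0% | 96.8% | 9.3 | 1.56 |

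The degree of freedom spent on the covariate changes these powers by less than 0.1 percentage point.

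**Step 4: what the normality switch does.** This was simulated with 8,000 runs, 31 per arm and SD 23. A Shapiro–Wilk test at 5% in either arm triggered the rank test; that criterion is assumed, since the protocol names none. The skewed case is a reversed gamma distribution with shape 2.

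| Data | Quantity | Always t | Always Mann–Whitney | Switch |
|---|---|---|---|---|
| Normal | Type I error | 0.045 | 0.043 | 0.045 |
| Normal | Power, difference 17 | 0.817 | 0.796 | 0.815 |
| Left-skewed | Type I error | 0.051 | 0.046 | 0.048 |
| Left-skewed | Power, difference 17 | 0.803 | 0.902 | 0.901 |

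The switch does not inflate type I error. It costs 0.002 of power with normal data and gains 0.098 over the t-test in this skewed case.

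**Step 5: P value against interval.** The usual 95% interval for a difference in means excludes zero exactly when the t-test is significant. In the skewed case with a true difference of 17, the two tests reject in 0.902 and 0.803 of runs. They must therefore disagree in at least 0.902 − 0.803 = 0.099 of runs. About 94% of runs took the rank branch there, so a rank P value beside a means interval that says otherwise is a practical possibility. The frequency depends on the shape of the data, and this is one assumed shape.

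**The case against.** The strongest reply is that nothing in {20a} is invalid. Randomisation makes the unadjusted comparison unbiased, its standard error already allows for chance baseline imbalance, and the trial was sized for exactly this test. That stands. A reader might infer that the trial is underpowered, the sample size wrong or the estimate biased; Steps 1 and 2 do not support any of these.

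A reader might also infer that the normality check itself wastes power or inflates type I error. Step 4 does not support that. The lost efficiency comes only from leaving out baseline, and the harm from the switch is to pre-specification and to the quantity being estimated.

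The size of the gain is conditional. The background says only that low preoperative scores can be predictive. It gives no coefficient and no link to 24 h or 48 h scores in these patients. At r = 0.2 the gain is about 1.5 percentage points. Section {20c} expects very little missing primary data; if all 35 per arm are evaluable, the unadjusted test already has 86.2% power and the gain at r = 0.5 falls from about 9 to about 8 points. All of this stands.

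Finally, covariates and the criterion for normality are often left to an analysis plan. The lack of a named criterion is therefore not counted here. But {20a} does state the tests, the summaries and the interval, and the mismatch between the rank branch and the means interval lies in that stated text. A later plan that adjusted for baseline would depart from it.

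**Conclusion.** The point holds as two moderate weaknesses in a stated method; neither is an error that invalidates the trial.

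First, precision is given up at almost no saving. From 82% unadjusted with 31.5 evaluable per arm, power would be about 84%, 86%, 92% or 95% at correlations of 0.2, 0.3, 0.5 or 0.6, and the interval would be about 2%, 5%, 13% or 20% narrower. These figures rest on the planning difference and SD and on a correlation the protocol does not give. That the covariate is collected, called predictive and left unused rests on the text alone.

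Second, the primary test is undetermined until outcomes are seen, and the rank branch does not match the promised interval. This needs no assumption beyond the wording of {20a}; only its frequency does.

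The change should be made, but the trial can still give a valid answer without it.

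**What to change.** Amend {20a}, before unblinding, as follows:

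- Analyse QoR-40 total by ANCOVA with arm and baseline QoR-40 total as terms, in the same way at 24 h and 48 h. Section {12} names both as primary; this change does not rank them.
- Report the adjusted mean difference with a 95% confidence interval (robust or bootstrap), and take the P value from the same model, so that the two address one quantity.
- Remove the normality-based choice of test for the primary outcome.
- Keep the unadjusted t-test and Mann–Whitney U as sensitivity analyses.

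The cost is one degree of freedom. No new data, visits or patients are needed, and the sample size can stay as it is. Because {20a} is protocol text, the change has to go through the amendment route in {25}, including the ethics committee. With 50 of 70 participants already recruited when the article was written ({15}), it should be made promptly and dated.

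### For outcomes tested by Mann–Whitney and shown as medians, the plan still prescribes a confidence interval for the difference in means, so the interval matches neither the test nor the summary

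*Protocol article*

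**What the plan says.** All of this stands in the protocol article under Statistical methods for primary and secondary outcomes {20a}.

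- Normal branch: "All normally distributed continuous variables will be expressed as mean ± standard deviation and analyzed with Student’s" t-test.
- Non-normal branch: "For non-normal distributed data, the Mann–Whitney" U test is used, and "results will be presented as median and interquartile interval".
- Effect interval, stated once for both branches: "A 95% confidence interval (CI) for differences in means (for continuous outcomes) or relative risks (for categorical outcomes) will be calculated".
- Significance is declared at P < 0.05. The interval is given no role in that decision.

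The section names no rank-based or median-based interval.

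**The concern.** The sentence on intervals divides outcomes into only two classes, continuous and categorical, and gives every continuous outcome a difference in means. The sentences before it have already split continuous outcomes into a mean-based branch and a rank-based branch. An outcome on the rank-based branch would thus be reported with three quantities that need not agree: a test on ranks, a pair of medians, and an interval for means.

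The outcomes most likely to take that branch are listed under Outcomes {12}: PCA use, opioid consumption, rescue analgesia, and VAS at four times. QoR-40 follows the same rule if it is judged non-normal. A results table could then show P < 0.05 beside an interval that includes zero, or the reverse, or a mean difference whose sign opposes that of the medians. A reader could not tell how large the effect is or how precisely it was estimated.

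**Working it through.** **1. The plan's own figure.** Sample size {14} gives the inputs: "mean of group 1 was 167 and the mean of group 2 was 184", "with known group standard deviations of 23", two-sided alpha 0.05, power 80%, dropout 10%.

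n per arm = 2 × (1.960 + 0.842)² × 23² / 17² = 28.7, rounded up to 29. Then 29 / 0.9 = 32.2, rounded up to 33.

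The stated 33 per group reproduces. The point does not depend on it, but the planned 35 per arm is used below.

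**2. Test, summary and interval side by side**

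| Branch | Test | Summary | Interval | Same quantity? |
|---|---|---|---|---|
| Normal | t-test (means) | mean ± SD | difference in means | yes |
| Non-normal | Mann–Whitney (ranks) | median, interquartile interval | difference in means | no |

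**3. A constructed data set, 35 per arm.**
- Arm A: ten 0s, ten 1s, ten 2s, and 3, 3, 4, 30, 40. Total 110, mean 110/35 = 3.14, median 1.
- Arm B: three 0s, six 1s, twelve 2s, eight 3s, six 4s. Total 78, mean 78/35 = 2.23, median 2.
- Mann–Whitney P = 0.005, with arm A lower.
- Difference in means = 3.14 − 2.23 = 0.91. Sample variances are 65.83 and 1.42, so the standard error is √((65.83 + 1.42)/35) = 1.386. With t(68) = 1.995, the 95% CI is 0.91 ± 2.77, or −1.85 to 3.68.

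The interval includes zero, and its point estimate has the opposite sign to the difference in medians.

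**4. How often they disagree.** Trials with 35 per arm were simulated, 4,000 to 20,000 per scenario. Disagreement means that Mann–Whitney P < 0.05 and the pooled-t 95% CI excluding zero do not coincide. The document gives no distributions, so every shape is an assumption. For negative binomial counts, variance = mean + mean²/k.

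| Assumed scenario | Disagreement |
|---|---|
| Counts, means 10 vs 6, k = 1 | 16.4% |
| Counts, means 10 vs 6, k = 2 | 11.0% |
| Counts, means 9 vs 5, k = 1 | 16.9% |
| Counts, means 2 vs 1, k = 0.7 | 15.7% |
| Counts, means 1.5 vs 0.7, k = 1 | 14.3% |
| Left-skewed QoR-40, target means 184 vs 167, SD 23, ceiling 200 assumed | 13.5% |
| Log-normal, log-SD 1, median ratio 1.74 | 23.7% |
| Normal, 184 vs 167, SD 23 | 4.5% |
| Identical log-normal arms (no effect) | 4.9% |
| Counts, means 10 vs 3 (large effect), k = 1 | 2.6% |
| Counts, means 10 vs 3 (large effect), k = 2 | 0.1% |

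The direction varies. With counts it is mostly P ≥ 0.05 beside an interval excluding zero. With log-normal data it is mostly the reverse. In the left-skewed QoR-40 case every disagreement has P < 0.05 beside an interval including zero.

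In one further assumed case, with equal means but different skew, disagreement is 28.6%. There the two methods answer different questions, and only the ranks differ between arms.

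**The case against.** **The interval may be meant only for outcomes summarised by means.** The section ties means to the normal branch, so this reading is possible. Rank-tested outcomes would then simply lack a stated interval, a detail that an article may leave to a fuller plan. But the text does not restrict the sentence in that way. It sets continuous against categorical and leaves no third class, so followed as written it covers the rank-tested outcomes.

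**The disagreement rates are not error rates.** This stands. They are highest near middling power: for counts of 10 vs 6 with k = 1, Mann–Whitney has about 40% power and the t-test about 49%. Any two valid tests part company on borderline results, as the 4.5% for normal data shows. The pooled-t interval is also an assumption, because the protocol does not say how the interval is computed.

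**A mean-difference interval can be approximately valid at 35 per arm even with skewed data.** This also stands. The fault lies in the pairing, not in the interval itself.

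**The Hodges–Lehmann estimate is not the difference between the two medians shown.** Correct. It is the median of all pairwise differences, but it does belong to the same rank method as the test.

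**The reach is mostly secondary outcomes.** Largely true. The primary QoR-40 was sized on means and is affected only if it is judged non-normal.

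**Conclusion.** The point holds as a mismatch in a stated rule and should be corrected before analysis. It does not threaten the validity of the trial. For skewed continuous outcomes the prescribed interval corresponds to neither the test nor the summary. It can contradict the P value in about 11 to 24% of trials under the assumed skewed shapes with moderate effects, and in about 5% or fewer with no effect or a large one. Those rates rest on assumed distributions and on 35 analysed patients per arm. The mismatch itself rests only on the wording.

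A reader might infer two stronger things that the document does not support:

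- That the analgesic conclusion depends on whether the P value or the interval is quoted, or that the false-positive rate rises. The section fixes P < 0.05 as the criterion and gives the interval no decision role, so neither follows.
- That the relative risk for categorical outcomes fails when an arm has no events. With no events in the SAPB arm, the ratio of SAPB to control is 0, and a score interval exists (0/35 vs 4/35 gives 0 to 0.92). Only the log-based Wald formula breaks down, and the protocol does not name it. The protocol also gives no event rate from which to judge how likely an empty arm is.

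**What to change.** State in {20a} that the P value and the 95% CI for each continuous outcome come from the same method:

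- t-test: difference in means with its CI, as now.
- Mann–Whitney: Hodges–Lehmann shift with its 95% CI, in place of the mean-difference CI. Add that it estimates the median of pairwise differences and reads as a shift only if the two arms have similar shapes.
- Heavily tied counts, such as rescue doses: a mean-based test with a matching interval, namely a permutation P value with a bootstrap CI for the mean difference.

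The cost is a few sentences and a few lines of analysis code, with no extra patients or data. The downside is slight extra analysis work and the shape caveat. The article describes recruitment as still under way, so the wording can be settled before the data are analysed.

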#### Interim analyses {21b}

No interim analyses will be conducted due to the small number of patients and the expected low incidence of serious adverse events.

#### Methods for additional analyses (e.g., subgroup analyses) {20b}

No subgroup analyses are planned.

#### Methods in analysis to handle protocol non-adherence and any statistical methods to handle missing data {20c}

The likelihood of missing values in our primary outcome is very low. If missing data occur, multiple imputation techniques will be employed to accurately estimate them.

#### Plans to give access to the full protocol, participant-level data, and statistical code {31c}

Data sets, statistical codes, and complete protocols analyzed by the institute will be available upon reasonable request to the principal investigator. This approach ensures accuracy, repeatability, and promotes further study and cooperation.

### Oversight and monitoring

#### Composition of the coordinating center and trial steering committee {5d}

The steering committee, composed of principal investigator, sub-investigator, and two clinicians, will guide and supervise the implementation and progress of the trial. Quarterly meetings will be convened to monitor the latest developments in the trial, ensuring that the research design and interpretation remain relevant to current clinical practice. The committee has the authority to make decisions regarding trial modifications based on specific circumstances and assumes medical responsibility for the patients involved.

